## Abstract

**Background:** Antenatal care (ANC) in many low- and middle-income countries is under-utilized and of sub-optimal quality. Group ANC (G-ANC) is an intervention designed to improve the experience and provision of ANC for groups of women (cohorts) at similar stages of pregnancy.

**Methods:** A two-arm, two-phase, cluster randomized controlled trial (cRCT) (non-blinded) is being conducted in Kenya and Nigeria. Public health facilities were matched and randomized to either standard individual ANC (control) or G-ANC (intervention) prior to enrollment. Participants include pregnant women attending first ANC at gestational age <24 weeks, health care providers, and sub-national health managers. Enrollment ended in June 2017 for both countries. In the intervention arm, pregnant women are assigned to cohorts at first ANC visit and receive subsequent care together during five meetings facilitated by a health care provider (Phase 1). After birth, the same cohorts meet four times over 12 months with their babies (Phase 2). Data collection was performed through surveys, clinical data extraction, focus group discussions, and in-depth interviews. Phase 1 data collection ended in January 2018 and Phase 2 concludes in November 2018. Intention-to-treat analysis will be used to evaluate primary outcomes for Phases 1 and 2: health facility delivery and use of a modern method of family planning at 12 months postpartum, respectively. Data analysis and reporting of results will be consistent with norms for cRCTs. General estimating equation models that account for clustering will be employed for primary outcome analyzes.

**Results:** Overall 1,075 and 1,013 pregnant women were enrolled in Nigeria and Kenya, respectively. Final study results will be available in February 2019.

**Conclusions:** This is the first cRCT on G-ANC in Africa. It is among the first to examine the effects of continuing group care through the first year postpartum.

**Registration**: Pan African Clinical Trials Registry
PACTR201706002254227 May 02, 2017

## Background and study rationale

The primary purpose of antenatal care (ANC) is to help women have a healthy pregnancy and safe delivery
^1^. Through ANC, health care providers can identify emergent complications of pregnancy, but ANC also serves as a primary health care platform for identification of underlying chronic health issues and support for healthy behaviors and preventive measures, such as oral iron supplementation, use of long-lasting insecticidal nets (LLIN), tetanus immunization, and counseling for postpartum family planning (PPFP)
^2^. ANC often serves as an entry point for further interaction with the health system. Both multiple ANC visits and high-quality ANC contacts are positively associated with facility delivery and skilled birth attendance
^3–
5^.

Current service delivery models in low- and middle-income countries (LMICs), where the greatest proportion of maternal, perinatal, and newborn deaths occur, may not allow for optimal provision of all curative, preventive, and promotive services
^6–
8^. Globally, according to
UNICEF, 86% of pregnant women attend one antenatal care visit (ANC1) with a skilled provider, and 62% attend four or more visits (ANC4). Inadequate ANC attendance can partially be explained by poor provision and experiences of care
^9–
12^. Most women do not receive the full range of recommended ANC services
^13–
15^. Women report long wait times, unpleasant experience with providers, lack of provider attentiveness, lack of privacy, and limited provision of services, all of which result in low client satisfaction
^16–
18^. Contact with providers may be brief, as reported in Tanzania where the average contact time was 12 minutes for the first contact and 6.5 minutes for subsequent visits
^19^. Health care providers face numerous barriers to providing high-quality ANC (e.g., poorly resourced work environments, heavy workloads, long working hours), which cause stress, poor job satisfaction, and uncaring behavior toward clients
^20,
21^.

Group ANC (G-ANC) is an alternative ANC service delivery model. Where implemented, G-ANC is described and offered as an alternative to individual care when women come to their first ANC visit. Women who choose G-ANC are placed in groups, or cohorts, with other women of similar gestational age (GA) and receive subsequent ANC together during scheduled meetings facilitated by a health care provider at the health facility. Implementation and research on G-ANC to date has primarily been in high-income countries
^22,
23^. These studies found that, when compared to individual ANC, G-ANC resulted in increases in several outcomes: uptake of family planning at 6, 9, and 12 months postpartum; length of gestation; birth weight; breastfeeding initiation and duration; attendance at ANC; health literacy; and patient satisfaction; as well as decreased transmission of sexually transmitted infections during pregnancy
^24–
26^. A Cochrane review in 2015 was not conclusive on the health outcomes of the intervention, however, it found participants viewed G-ANC positively, and no negative outcomes for mothers or their babies were identified
^27^.

This evidence was considered by the World Health Organization (WHO) in the development of new ANC recommendations in 2016. Those recommendations state that G-ANC may be offered as an alternative to individual ANC in the context of rigorous research
^2^. To date, there have been a limited number of studies on the effect of G-ANC in LMICs, primarily from single site studies in Malawi, Tanzania, Nigeria, and Ghana
^28–
34^. Available results indicate acceptability and feasibility, but the single site nature of these studies limits generalizability.

We therefore designed a cluster randomized controlled trial (cRCT) to test the feasibility, acceptability, and effectiveness of G-ANC in multiple facility contexts, including a mix of urban, peri-urban, and rural sites, in two African countries. The cRCT design enables implementation in sites with lower ANC census numbers than would be necessary for an individually randomized study (i.e., twice the census would be needed to form cohorts while individually randomizing). In addition, the cluster design decreases the risk of contamination between study arms.

The study will be conducted in two phases. The primary outcome of Phase 1 is an increase in the percentage of women who have a facility-based delivery. In Phase 1, the study will test whether re-organization of care from individual ANC to G-ANC, and the corresponding emphasis on participatory care and learning, will: improve the provision and experience of ANC; empower women and health care providers; and increase health literacy—together, leading to greater practice of healthy behaviors and health service utilization among women experiencing group care. The primary outcome for Phase 2 is an increase in the use of a modern family planning (FP) method at one year after birth. In Phase 2, the study will test whether women who remain in the same cohorts and receive care in groups for the first year postpartum report improved practice of health, hygiene, and early childhood development behaviors and increased health service utilization. Outcomes are measured at the individual participant level.

## Methods

### Study design

The study is a multi-country, two-phase, cRCT implemented in Machakos and Kisumu Counties, Kenya and in Nasarawa State, Nigeria. It was designed in collaboration with the Kenyan Ministry of Health (MOH) and the Nasarawa State MOH and Primary Health Care Development Agency in Nigeria.

In each country, 20 health facilities were selected and matched in pairs by: type of health facility (e.g., health center, hospital); client caseload for first ANC visit (i.e., ANC1); location (urban, peri-urban, rural); culturally similar catchment populations; and availability of FP services. The pairs had to be either within the same state (Nigeria) or county (Kenya), but did not need to be geographically adjacent. In Kenya, 10 clusters were assigned to each of the two counties where the study took place.

The unit of randomization was the health facility, which formed the clusters. For each pair of matched health facilities, randomization (1:1) was done to the intervention (group care) or control arm (the current standard of individual care according to country guidelines). Assignment to study arms was done through a lottery using pieces of paper in a basket bearing the words “intervention” or “control”.

In both study arms, all women provided written consent to participate in the study. In each health facility, 50–54 participants were consented and enrolled, along with three health care providers. For the intervention arm, four to five cohorts (groups of women) were formed per facility.
Figure 1 summarizes the study design.

**Figure 1. f1:**
[figure not shown]
Study design. Description of randomization to intervention and control group and the intervention package for each study group.

### Study setting

The study is being implemented in Machakos and Kisumu Counties in Kenya and in Nasarawa State, Nigeria. Countries were chosen based on interest to the funder. In-country locations were chosen in collaboration with local colleagues, based on adequate security for women to travel to ANC; functional local health system governance and structure; Jhpiego’s ability to leverage existing maternal, newborn, and child health/FP (MNCH/FP) projects to reduce implementation costs; and where possible, avoidance of other ongoing projects that could introduce bias.
Table 1 presents key indicators for Kenya and Nigeria, comparing the national and state/county-level indicators in each country as appropriate
^35,
36^.

**Table 1. T1:** Comparison of key MNCH/FP indicators for Kenya and Nigeria. Summary of key maternal newborn and child health/family planning (MNCH/FP) indicators based on DHIS2 data for Kenya (Kisumu and Machakos Counties) and Nasarawa, Nigeria.

	Kenya (DHS 2014)			Nigeria (DHS 2013)	
Indicator	National	Kisumu County	Machakos County	National	Nasarawa State
Maternal mortality ratio (per 100,000)	362	na	na	576	na
Neonatal mortality rate (per 1,000)	22	na	na	37	na
No ANC	3.9%	1.3%	1.0%	33.9%	na
Any ANC from a skilled provider	95.5%	98.4%	98.8%	60.6%	63.2%
ANC4	57.6%	na	na	51.1%	na
Median GA at first ANC	5.4 months	na	na	5.0 months	na
Birth with skilled provider	61.8%	69.2%	63.4%	38.1%	40.7%
Birth in a health facility	61.2%	69.5%	62.9%	35.8%	40.1%
Postnatal care (PNC) within 2 days (mother)	52.9%	na	na	39.6%	49.4%
PNC within 2 days (baby)	35.6%	na	na	14.0%	18.9%
Exclusive breastfeeding	61.0%	na	na	17.0%	
Contraceptive prevalence rate (modern method), currently married	53.2%	na	na	9.8%	16.3%

na = data not available—maternal mortality ratio and neonatal mortality rate are computed only at national level. DHS = Demographic and Health Survey

In 2016, Kenya had an estimated population of
45 million. Machakos and Kisumu County populations were
1.1 million and
0.96 million, respectively. While ANC attendance is nearly universal, fewer than six in ten (57.6%) pregnant women attend four or more visits during pregnancy
^35^. The facility-based delivery is 61.2% nationally, 62.9% in Machakos County, and 69.5% in Kisumu County
^35^. Nationally, 52.9% of women receive PNC within two days of giving birth
^35^. FP use among postpartum women was estimated at 36% based on analysis of 2008–2009 Kenya Demographic and Health Survey (DHS) data
^37^.

Nigeria is the most populous nation in Africa, with an
estimated 198 million inhabitants. Nasarawa State has an estimated population of
2.5 million. One-third of pregnant women (33.9%) in Nigeria do not receive any ANC
^36^. Half (51.1%) receive four or more ANC visits
^36^. The facility-based delivery rate is 35.8% nationally and 40.1% in Nasarawa State
^36^. Both ANC and delivery with a skilled birth attendant coverage have stagnated
^38^. Quality of ANC is poor
^39^. PNC within two days is 39.6% for the mother and 14.0% for the newborn
^37^. FP use among postpartum women was estimated at 15% based on analysis of 2008 Nigeria DHS data
^37^.

Both countries have national policy documents that promote key evidence-based MNCH/FP interventions—at least four ANC visits and a facility-based delivery with a skilled provider
^40–
44^.

### Participants

***Eligibility for clusters.*** The intervention is multilevel with activities targeted to different participants in the selected health facilities.

**Health facilities (clusters):** A list of health facilities offering ANC and postnatal care (PNC) services in each study location was prepared by the study team, based on data from the national health information systems (HIS), which use the open source software platform
District Health Information System 2 (DHIS2). Within the study areas, at the time of site selection, 551 health facilities in Nigeria and 410 in Kenya were providing ANC services. Study criteria dictate that women in group care need to be 20–24 weeks GA at the time of the first group meeting, thus a minimum ANC1 census was deemed the most important criteria to determine the ability to form cohorts. HIS data for the 12 months preceding the study was used to identify potential sites. In Nigeria, all facilities with more than 20 new ANC clients/month who initiated care at or before 20 weeks GA were considered for inclusion. GA at ANC1 was not available in the Kenya HIS. Therefore, assuming approximately 50% of women enter care < 24 weeks (participant criteria), all facilities with a minimum of 30 new ANC clients/month were considered. Members of the study team then visited all facilities to verify HIS ANC census numbers, by examining the ANC registers for the previous three months, and to verify additional selection and matching criteria. Facilities were selected in conjunction with county/state health officials and included consideration of “best match” ability as well as inclusion of urban/peri-urban/rural sites and varied levels of the health system (
Table 2).

**Table 2. T2:** Eligibility for health facilities and participants. Description of the inclusion criteria for health facilities and participants included in the study.

Category	Inclusion Criteria
**Health facilities**	• Located in one of the selected two counties in Kenya, or Nasarawa State in Nigeria • A minimum of new ANC clients monthly: 30 clients in Kenya; 20 clients ≤ 20 weeks GA in Nigeria • Availability of community health extension workers (CHEWs), government employed facility-based staff • A minimum of two staff during all working hours • On-site availability of ANC, PNC, and FP services • Permission granted by health facility management to participate in study • Public health facility
**Pregnant women**	• Minimum age of 15 years at the time of enrollment * • Appropriate GA as best estimated by provider using combination of last menstrual period, pelvic exam, fundal height, quickening, ultrasound, and/or timing of fetal heart tones dependent on availability o Control sites: < 24 weeks GA o Intervention sites: Between 20–24 weeks GA at the time of first group meeting; and reply “yes” or “unsure” when asked if can return for first cohort meeting • Willing and able to provide a phone number through which she can be reached • Detailed locator information for follow-up (all who provide cell phone number AND also for those without cellphone but traceable). • Planning to stay in area for the next year, and not planning to be away from home (near this facility) for more than four weeks in a row at any time during pregnancy or more than three months in a row in the year after the baby is born • Willing to participate and consent to follow-up for up to 12 months post-delivery
**Health care** **providers**	• Working in a participating/selected health facility and providing ANC or PNC services • Willing to participate in the study
**Sub-national health** **managers**	• Working in the study state or county as a government official managing health activities and/or service delivery • Willing to participate in the study

*Note, In Kenya, pregnant women under the age of 18 are considered mature minors and are able to give consent for themselves, if they can demonstrate evidence of clear understanding of the requirements for the research they are consenting to participate in Kenya
^45^. In Nigeria, persons aged 13 and above can consent for themselves (i.e., without parental consent) to participate in non-therapeutic research
^46^.

***Eligibility for participants.*** Study participants include pregnant women, health care providers, and sub-national health managers. The inclusion criteria are detailed in
Table 2. There were no additional exclusion criteria.

**Pregnant women**: Pregnant women 15 years and older attending ANC1 in any of the study health facilities. Additional criteria on GA and availability were applied depending on the study arm.

**Health care providers:** Providers working in the participating health facilities primarily providing ANC and PNC services.

**Sub-national health managers:** Included either government officials who work in sub-national level health management positions or health facility in-charge in study settings.

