### Intervention

The intervention is provision of an alternative service delivery model that delivers care in a group, compared to the current standard of care provided individually (i.e., one-on-one between a provider and an ANC client). Women in the intervention arm were invited to attend five G-ANC meetings in addition to the first visit (Phase 1) and four Healthy Mother, Healthy Baby (HMHB) meetings (Phase 2) in the year following birth.

***Phase 1: G-ANC.*** At the first ANC visit (ANC1), pregnant women are assessed for GA. If eligible, women in the intervention group are offered the option of G-ANC for their subsequent ANC. Interested women are placed in a cohort of 8–15 other women of similar GA, all of whom will be 20–24 weeks pregnant at the time of a pre-scheduled cohort start date (Meeting 1). Thereafter, they attend subsequent routine visits together every month as G-ANC meetings. Five total scheduled meetings are held and recorded as ANC contacts, each lasting approximately two hours.

In each intervention facility, two ANC providers (nurses or midwives) and one CHEW were trained as G-ANC facilitators. In both countries, CHEWs are facility-based and provide some level of clinical care. Two facilitators were assigned to each cohort and were advised to co-facilitate meetings for that group throughout the intervention.

Prior to initiating the study, inputs were made to all facilities, in both arms, in the same quantities, to ensure comparable capacity for service delivery (
Table 3). The inputs included a select set of ANC commodities that would ordinarily be provided through the public sector health system. In addition, a one- to two-day refresher training on ANC and PPFP counseling was provided for all ANC providers at control sites and for G-ANC facilitators at intervention sites. Intervention facilities received additional G-ANC specific inputs as outlined in
Table 3.

**Table 3. T3:** Inputs provided to control and intervention clusters. Description of the elements of support provided to the two study arms in accordance to the group assignment.

Input	Intervention Clusters (Group Care)	Control Clusters (Current Standard Individual Care)

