In the intervention arm, assignment to a cohort was done based on GA at the time of the pre-determined cohort start date (i.e., Meeting 1). Eligible women unable to attend the first meeting were not consented or assigned to a group; they were advised to continue with standard individual ANC. If a woman was eligible for the study, but there were no open cohorts (e.g., the appropriate cohort was full), she was advised to continue with standard individual ANC. In the control arm, all eligible women who were willing to participate were consented. Written consents were obtained for all study participants in their language of choice (from the five options). A baseline survey was administered immediately after the consent process.

If it was not possible to recruit a minimum of eight women at least three days before the scheduled cohort start date, the cohort was cancelled, and the assigned women re-evaluated for eligibility into another cohort. Women who become ineligible to participate due to cohort cancellation were advised to continue with standard individual ANC. Their data were then coded to reflect cohort cancellation and retained for reporting purposes. However, they were removed from the study sample, and no additional follow-up was done for these women.

***Sub-national health managers and health facility in-charge.*** Sub-national health managers (i.e., county-level in Kenya; state-level in Nigeria) responsible for overseeing reproductive health programs were recruited by study staff via phone at the end of Phase 1 to participate in the in-depth interviews (IDIs). Priority was given to managers known to have had exposure to G-ANC at the end of Phase 1. An appointment for a face-to-face interview was scheduled with each respondent.

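### Women were recruited after facility allocation was known, with extra attendance-related rules in the intervention arm only; randomisation does not protect their comparability, and adjusting for observed baseline imbalances does not repair this

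*Protocol article*

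**What the plan says.** The Abstract puts allocation before recruitment: "Public health facilities were matched and randomized to either standard individual ANC (control) or G-ANC (intervention) prior to enrollment". Study design adds that "The unit of randomization was the health facility, which formed the clusters". The trial is non-blinded, and Recruitment and consent says that providers, who refer women for screening, knew the assignment.

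Table 2 sets two rules on GA. For control it reads "Control sites: < 24 weeks GA". For intervention it reads "Between 20–24 weeks GA at the time of first group meeting", together with a yes or unsure answer "when asked if can return for first cohort meeting". The text under Eligibility for participants confirms that GA and availability criteria depended on the arm. The other criteria in Table 2 are common to both arms: age, phone or locator details, plans to stay in the area, and agreement to follow-up.

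The intervention arm has further steps. Under Intervention, Phase 1, "Interested women are placed in a cohort of 8–15 other women of similar GA". Under Recruitment and consent, "Eligible women unable to attend the first meeting were not consented or assigned to a group", whereas "In the control arm, all eligible women who were willing to participate were consented". An eligible woman with no open cohort was sent back to individual care. If a cohort fell short of eight women it was cancelled and its members were reassessed for another. Those no longer eligible were dropped from the sample and not followed up.

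Data analysis states intention-to-treat and a logistic GEE model that corrects for baseline differences between the arms. Maternal age is the only potential confounder given by name.

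**The concern.** Randomising facilities balances facilities, in expectation. It balances women only if they enter by the same rule in both arms, or before the arm is known. Neither condition holds here.

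The filter is also not neutral with respect to the Phase 1 outcome. The article's Background cites a positive association between multiple antenatal visits and facility delivery. Its Data quality assurance section says that Nigerian women tend to give birth where they receive antenatal care. A screen on whether a woman can and wants to come back to that facility is therefore plausibly a screen on facility birth. The same willingness may bear on contraceptive use at 12 months. Part of an observed difference could then be selection, and the Discussion expects these results to inform policy on adoption.

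**Working it through.** **1. Entry rules side by side.**

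| Step | Intervention | Control |
|---|---|---|
| GA at first visit | under 24 weeks | under 24 weeks |
| GA at Meeting 1 | 20–24 weeks on a pre-scheduled date | none |
| Able to return for Meeting 1 | yes or unsure; unable means not consented | not asked |
| Interest | in group care | in joining the study |
| Capacity | an open cohort | none |
| After assignment | removed if cohort cancelled and no other fits | none |
| Age, phone/locator, residence, follow-up | same | same |

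The return question and the inability rule may be one filter described twice, so I count them once. Cohort capacity depends on arrival date and has no evident link to facility birth. Attendance and interest carry the argument.

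**2. The GA rules refer to different dates.** Under 24 weeks applies at the first visit; 20–24 weeks applies at Meeting 1. No lower limit at enrolment is stated for either arm, and an early booker could in principle wait for a later cohort. The dates in Study status limit this somewhat:
- Meeting 5 (36–40 weeks) falls 16 weeks after Meeting 1 (20–24 weeks).
- Nigerian meetings ended in May 2017, so the last Meeting 1 was by about early February 2017 if the schedule was kept. A woman at 10 weeks on 1 January would then have been about 15 weeks. She fits no intervention cohort but meets the control rule.
- A woman at 10 weeks in October 2016 could have joined a cohort starting in January.

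Overlap is thus partial and cannot be measured from the article. If controls did book earlier, they had more time for visits. By the Background's own association that would work against group care.

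**3. The plan's sample size.** Inputs from Sample size: 61% (Kenya) and 40% (Nigeria), a 15-point difference, power 85% and 80%, design effect 2.45, attrition 20%. Two-sided alpha of 0.05 is my assumption. With pooled variance:
- Kenya: 171 per arm; 2 × 171 × 2.45 / 0.8 = 1,047, against 1,026 stated.
- Nigeria: 173 per arm; 2 × 173 × 2.45 / 0.8 = 1,060, against 1,076 stated.

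Both agree within about 2%, so the arithmetic is not at issue. It presumes, however, that the arms differ only by the intervention.

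**4. Illustration of selection.** Let *s* be the share of women who would enrol under control rules but be screened out under intervention rules. Let *g* be how far their facility-delivery rate lies below that of the women kept, *p*. With no true effect, the intervention arm has *p* and the control arm has (1 − *s*)*p* + *s*(*p* − *g*) = *p* − *sg*. The spurious difference is *s* × *g*. Neither value is in the article.

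For the false-positive rate I took the stated sample size less 20%, divided by 2 and by 2.45. This gives an effective 167.5 women per arm in Kenya (1,026 × 0.8 / 2 / 2.45) and 175.7 in Nigeria (1,076 × 0.8 / 2 / 2.45). The comparison is unadjusted, by normal approximation.

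| *s* | *g* (points) | Bias (points) | Share of 15 | False-positive rate, Kenya / Nigeria |
|---|---|---|---|---|
| 10% | 10 | 1 | 7% | 5.4% / 5.4% |
| 20% | 20 | 4 | 27% | 11.8% / 11.8% |
| 30% | 20 | 6 | 40% | 20.8% / 20.5% |
| 40% | 20 | 8 | 53% | 33.5% / 32.6% |

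**5. Cancelled cohorts.** Women already assigned in an intervention facility were removed from the sample. No equivalent step exists in control. An analysis by allocated group would retain them, so this rule and the stated intention-to-treat principle conflict.

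**The case against.** Much can be said on the other side, and several parts of it stand.

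- A reader might infer that the arms are not comparable. The article does not show that. It reports no baseline data and the flowcharts are not reproduced in the text available. What can be said is that comparability is unprotected.
- The filters are softer than they look. Unsure answers were accepted, and both arms faced the same demands on contact details, residence and 12 months of follow-up, which already select settled, cooperative women. This reduces the likely size of *g* but leaves a filter that only one arm applied.
- A reader might infer that controls booked earlier, and that comparisons of four or more visits or of miscarriage are distorted as a result. Step 2 shows that this is possible but not established, and that its effect on facility delivery could run the other way.
- The covariate list may sit in an analysis plan that is not shown. I accept this and do not rely on its absence. The point rests on the stated recruitment rules. The stated remedy responds to observed imbalance, and no list of measured covariates removes selection on motivation.
- Restricting the primary comparison to a common GA range would change the analysis population after Phase 1 data collection has ended, in a trial sized for only 80–85% power. I agree; this belongs in a sensitivity analysis.

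**Conclusion.** The point holds in this form: recruitment followed known allocation under rules that differed by arm, so randomisation does not protect the comparability of the women. The stated adjustment for baseline imbalances does not resolve this. The attendance and interest filters plausibly favour group care on facility delivery. Any GA difference at entry is uncertain in size and direction.

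The size is unknown. The range of 1–8 points (7–53% of the target) follows only from assumed values of *s* and *g*, in an unadjusted comparison. It should not be read as an estimate or as a bound. The removal of women from cancelled cohorts contradicts the stated intention-to-treat analysis whatever their number.

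**What to change.** Enrolment is closed, so the changes concern analysis and reporting.

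1. Make GA at the first antenatal visit a fixed covariate in both primary GEE models, whatever imbalance is observed. Recruitment and consent says that providers documented it for every new client.
2. Keep the full-sample analysis as primary. Add a sensitivity analysis restricted to the range of GA at enrolment found in both arms.
3. Where the counts were logged, report by arm the eligible women not enrolled (not interested, could not attend, cohort full) and the women removed because their cohort was cancelled. The article says that data on the cancelled-cohort women were retained; it does not say whether the other reasons were recorded by category. Reconcile the removal rule with intention-to-treat. Bound the effect of these exclusions under a stated range of assumptions. For cancelled cohorts, with *k* removed and *n* kept, the shift in the intervention-arm rate is *k*/(*n* + *k*) times the assumed outcome gap.
4. Limit the effectiveness conclusion to women willing and able to attend group care, and state that covariate adjustment cannot remove selection on unmeasured motivation.

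The cost is a few extra analyses and tables, and a narrower conclusion. The sample size does not change.
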